#### Recruitment

As of April 2022, 122 participants have been referred to the study. Participation is voluntary, and an extended informed consent form is signed before any evaluation, assessment, or voice and video call. Consent forms are collected remotely for those who have been discharged and are currently in remission and in person for those hospitalized in a COVID-19 ward of either pneumology, internal medicine, or infectious disease departments.

### Primary and Secondary Outcome Measures

#### Primary Outcome Measures

Efforts will be made to assess all participants who have completed the minimum required intervention activities. For DigiCOVID, the minimum required intervention activities include attending psychotherapy sessions at least 4 times. As the main goal of this project is to evaluate the feasibility, acceptability, and usability of DigiCOVID, we will conduct an analysis of the following primary outcome measures in all intention-to-treat (ITT) participants:

Assessment completion rate—based on our previous studies, we expect ≥80% of participants will complete the battery of web-based self-reports.Usability ratings obtained post DigiCOVID via a 7-point Likert scale questionnaire (ie, mean rating of all responses)—this is a brief and embedded poststudy questionnaire on program satisfaction, clarity, and perceived benefits. Participants will rate each sentence on the following 7-point Likert scale: 1=completely agree; 2=mostly agree; 3=somewhat agree; 4=undecided; 5=somewhat disagree; 6=mostly disagree; and 7=completely disagree. Based on our previous studies, we hypothesize exit survey ratings of at least ≥4.5 (SD 1.5) on the 7-point Likert scale items.Reported side effects (ie, raw score)—based on our previous findings, we expect 0 adverse events due to program use.Overall program completion rate—based on previous findings, we hypothesize full program completion in ≥70% study participants.

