#### Secondary Outcome Measures

The secondary outcome measures will be collected at baseline and immediately after the treatment for all participants. We designed DigiCOVID to improve mental well-being. Therefore, we will measure the impact of the intervention by looking at pre-post changes in the following outcome measures: the 12-item General Health Questionnaire [26] , the Impact of Event Scale–Revised [27], the 7-item General Anxiety Disorder scale [28], the Insomnia Severity Index [29], and the 9-item Patient Health Questionnaire [30]. We expected to observe a significant improvement across all these secondary outcome measures *P*< in both patients with COVID-19 and their family members. To verify these experimental hypotheses, we will conduct the analysis based on the preintervention (baseline) and postintervention data, using parametric and nonparametric statistical tests. The criterion for statistical significance is *P*<.05. Results with *P*<.1 will be described as trends.

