### Data Analysis

There are 3 a priori defined analysis populations, including a primary analysis population, a secondary analysis population designed to compare effect sizes in populations with no missing data, and a population who completed all study visits. The 3 populations are as follows:

ITT population: this is the a priori primary analysis population, defined as including all participants who attended at least 4 remote psychotherapy sessions.Intention-to-treat fully evaluable (ITT-FE) population: this is a secondary analysis population, defined as including all members of the ITT population who complete a postintervention visit. Note that a participant may complete a specific visit but have missing data for a test, in which case the participant is in the overall ITT-FE population but does not contribute data to the ITT-FE population for that visit (eg, the number of evaluable cases for a specific test on a specific visit may be smaller than the ITT-FE population for that visit because of missing data).Intention-to-treat completers (ITT-C) population: this is a secondary analysis population, defined as including all members of the ITT-FE population who complete all intervention sessions. Note that the ITT-C population is a strict subset of the ITT-FE population; a person who completes the treatment but does not complete the postintervention evaluation visit is not a member of the ITT-C population.

We also plan to perform different analyses in order to better describe the demographics of patients and relatives and to test whether there are significant differences in terms of response to our psychotherapy intervention.

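### Early leavers fall outside the usability and pre-post results, the article is inconsistent on who is assessed after treatment, and paired tests would make ITT and ITT-FE coincide on the symptom scales

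*Protocol article*

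**What the plan says.** **Who is assessed.** Primary Outcome Measures: "Efforts will be made to assess all participants who have completed the minimum required intervention activities". The next sentence defines the threshold: "the minimum required intervention activities include attending psychotherapy sessions at least 4 times". Eight sessions are offered. Secondary Outcome Measures says something different: "The secondary outcome measures will be collected at baseline and immediately after the treatment for all participants". The Methods place the repeat battery at the end of the therapy cycle and do not describe what happens for someone who stops after a session or two.

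**Who is analysed.** Data Analysis names ITT as the primary population, "defined as including all participants who attended at least 4 remote psychotherapy sessions". ITT-FE is "defined as including all members of the ITT population who complete a postintervention visit", and its stated purpose is a comparison of effect sizes in people without missing data. ITT-C narrows ITT-FE to those who completed every session. The primary outcomes (assessment completion, usability, side effects, program completion) are assigned to ITT.

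**How the scales are tested.** Secondary Outcome Measures: "we will conduct the analysis based on the preintervention (baseline) and postintervention data, using parametric and nonparametric statistical tests". The article does not say whether the tests are paired and names no method for missing values.

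**The concern.** There are two separate problems.

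The first is selection. The study's main purpose is to learn whether the program is feasible, acceptable and usable. Those who leave before session 4 are plausibly the ones who found it least acceptable or least helpful. The Limitations section points the same way: it reports poor motivation in some patients and attributes it to the remote format. If these people do not count in the usability rating or the pre-post change, both describe only those who stayed.

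The second is the planned comparison of populations. ITT-FE is meant to show what missing data do to the effect size. That works only if the ITT analysis uses something from members who lack a post-treatment score. A paired test uses nothing from them.

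**Working it through.** The article gives no sample size, power or effect figure on this point, so there is no stated number to reproduce.

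**1. The statements side by side**

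| Section | Group described |
|---|---|
| Primary Outcome Measures | assessment effort directed at those with at least 4 sessions |
| Secondary Outcome Measures | post-treatment collection for all participants |
| Data Analysis | ITT limited to those with at least 4 sessions |

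The first two rows differ on who is followed up. The third row excludes early leavers from the primary analysis however the first two are reconciled.

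**2. Possible size of the selection effect**

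All inputs are assumed: stayers improve by 0.40 SD; a share p leaves before session 4; leavers change by c, either 0 or a worsening of 0.2 SD. The article does not give p. Its expectation of at least 70% full completion would cap p at 30% if it refers to all starters, but that outcome is listed for analysis in ITT and may not refer to them.

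Change among all starters = (1 − p) × 0.40 + p × c. Excess = 0.40 / (change among all starters) − 1.

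| p | c | Change among all starters (SD) | Excess |
|---|---|---|---|
| 10% | 0 | 0.90 × 0.40 = 0.36 | 0.40/0.36 − 1 = 11% |
| 10% | −0.2 | 0.36 − 0.02 = 0.34 | 0.40/0.34 − 1 = 18% |
| 30% | 0 | 0.70 × 0.40 = 0.28 | 0.40/0.28 − 1 = 43% |
| 30% | −0.2 | 0.28 − 0.06 = 0.22 | 0.40/0.22 − 1 = 82% |

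**3. ITT against ITT-FE under paired tests**

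- A paired test on a scale uses people with both a baseline and a post-treatment value.
- ITT members with a post-treatment value are those who completed the postintervention visit and did not miss that test.
- Those are exactly the ITT-FE members who contribute to that scale.
- The two tests therefore use the same pairs and give the same result.

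One simulated data set (85 ITT members, 25 without a post-treatment score, missingness depending on baseline) illustrates this:

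| Method | ITT | ITT-FE |
|---|---|---|
| Paired t | −6.239, df 59 | −6.239, df 59 |
| Wilcoxon signed-rank | W = 204 | W = 204 |
| Random-intercept mixed model, mean change | −2.70 | −2.40 |
| Baseline carried forward, mean change | −1.70 | −2.40 |

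The populations separate only when the method keeps members without a post-treatment score. The data are invented; only the pattern matters.

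The identity extends in effect to the usability rating, which exists only after the program. It does not extend to the completion rates: completion of a post-treatment battery would be near 100% in ITT-FE by construction, and program completion has a different denominator in each set.

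**4. How many pairs would remain**

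Take the expected 80% battery completion as the post-treatment rate, and assume that 70% to 100% reach session 4.

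- From the 94 already tested: ITT 66 to 94; pairs 66 × 0.80 = 53 to 94 × 0.80 = 75.
- From the 122 enrolled: ITT 85 to 122; pairs 85 × 0.80 = 68 to 122 × 0.80 = 98.

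In both cases the pairs are about 56% to 80% of the starting group.

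**The case against.** The article does not say that people below 4 sessions go unassessed. It says where effort will be directed, and the phrase about all participants could mean both patients and relatives, or all ITT members. A reader might infer that early leavers will certainly have no post-treatment score and no usability rating. The text does not establish that, so this part is a conflict to reconcile and not a demonstrated loss of data. Still, singling out those with at least 4 sessions would serve little purpose if everyone were pursued equally, and the ITT definition excludes early leavers from the analysis whether or not their data are collected.

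The article also does not say that the tests are paired or complete-case. The exact test and the missing-data method may stand in a full protocol or SAP that is not shown, and a model or imputation would break the identity. This is right, and that part of the point is conditional. Paired tests on observed values are nonetheless the natural reading.

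A reader might further infer that the ITT analysis as a whole collapses into ITT-FE, or that the 4-session limit on follow-up causes the collapse. Neither is supported. The completion rates differ between the two sets, ITT-C remains a real comparison, and the identity comes from how ITT-FE is defined.

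Finally, the leaving rates and changes are assumed. At 10% leaving with no change among leavers, the excess is a modest 11%. There is also no control arm, so these figures describe a mean change and not a treatment effect.

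**Conclusion.** The point holds in limited form. The two outcome sections disagree on who is assessed after treatment. Independently of that, defining ITT by at least 4 sessions leaves early leavers out of the usability rating and the pre-post change, with a plausible bias in the program's favour. Under the assumed values the excess ranges from 11% to 82%. Its direction depends on leavers doing less well than stayers; if they improved as much, there would be none.

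If the tests are paired tests on observed values, the ITT versus ITT-FE comparison is empty for the five secondary scales and in effect for usability. That is certain given the condition, but the article does not state the condition. It does not support saying that early leavers are definitely unassessed, or that ITT and ITT-FE agree on every outcome.

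**What to change.** 1. Reconcile the two outcome sections. State that the post-treatment web battery and exit survey are sought from every participant assigned to a therapist, at the time of stopping or at the planned end of the cycle, whatever the number of sessions attended.
2. Redefine the primary (ITT) population as all participants assigned to a therapist with a baseline score. Relabel the group with at least 4 sessions as a minimum-exposure or per-protocol set. Without this step, data collected from early leavers would not enter the primary analysis.
3. Analyse the secondary scales with a method that keeps participants without a post-treatment score, for example a repeated-measures mixed model or multiple imputation. Keep ITT-FE and ITT-C as sensitivity analyses; ITT-FE then has a real comparator.

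The cost is small: a link and reminders for a battery that is already web-based, and a standard analysis method. The downside is a lower apparent response rate and possibly a smaller reported change. Recruitment is described as nearly complete, so assessment at stopping may no longer be possible for people who have already left. Steps 2 and 3 can still be applied to the data in hand.

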### Limitations

Some limitations have emerged as we operationalized this project. First, we observed a lack of motivation in some patients, likely caused by the remote technology-based approach. Second, even if telepsychiatry has been proven efficacious in assessing patients remotely, psychologists and psychiatrists are asked to adapt their methods of assessment, diagnosis, and treatment to new means of communication. The dissemination of this digital approach at a national level may require additional training for mental health professionals to ensure impact and effectiveness of this promising intervention.

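### Usability, a primary outcome, is assigned to the ITT population but can only be a mean among those who return the exit survey

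*Protocol article*

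**What the plan says.** Under Primary Outcome Measures, the protocol article states: "we will conduct an analysis of the following primary outcome measures in all intention-to-treat (ITT) participants". Usability is one of the four outcomes listed. Its measure is "Usability ratings obtained post DigiCOVID via a 7-point Likert scale questionnaire (ie, mean rating of all responses"), and the instrument is described thus: "this is a brief and embedded poststudy questionnaire on program satisfaction, clarity, and perceived benefits". The target is numeric: "we hypothesize exit survey ratings of at least ≥4.5 (SD 1.5) on the 7-point Likert scale items". The printed anchors run from 1 (completely agree) to 7 (completely disagree).

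Under Data Analysis, the ITT population is "defined as including all participants who attended at least 4 remote psychotherapy sessions". Members of that population who also complete a postintervention visit form a separate, secondary population, ITT-FE. The article notes there that the number evaluable for a given test may be smaller still because of missing data.

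The same outcome list expects at least 80% of participants to complete the self-report battery. For the program as a whole it says: "we hypothesize full program completion in ≥70% study participants".

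**The concern.** The population and the measure do not fit together. A person who attends 4 sessions is in the ITT population whether or not the exit survey is ever returned. Without a survey there is no rating, and because usability has no baseline value, a pre-post or mixed model has nothing on that person from which to estimate one. What is reported as an ITT result will be the mean of a subset, in effect the ITT-FE members who answered. The article's planned comparison of ITT with ITT-FE cannot expose this for usability, because the two means would rest on essentially the same people.

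This matters because usability is primary and has a numeric target. If those who do not answer would have rated the program differently, a statement that the ITT population meets or misses the target may be wrong. The article gives a reason not to take non-response as unrelated to the outcome. Its Limitations section reports: "we observed a lack of motivation in some patients, likely caused by the remote technology-based approach".

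**Working it through.** The article gives no sample size, power or test for usability, so there is no planned figure to reproduce. The check is how far a respondent mean can sit from the mean of the whole ITT population.

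**Inputs**
- SD 1.5 and target 4.5: Primary Outcome Measures.
- Missing fraction 20%: the complement of the 80% battery-completion benchmark. Missing fraction 30%: the complement of the 70% program-completion benchmark. Both are proxies, since neither is a rate of survey non-return.
- Difference between respondents and non-respondents: 0.75 to 1.5 points (0.5 to 1 SD). This is an assumption; the documents give no figure.
- n = 94: the number reported under Results as having completed tests and questionnaires. The time point is not stated and this is not the ITT count, so it is used only for scale.

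**Bias.** With respondent fraction r, ITT mean = r × (respondent mean) + (1 − r) × (non-respondent mean). Therefore respondent mean − ITT mean = (1 − r) × difference.
- 20% missing: 0.2 × 0.75 = 0.15; 0.2 × 1.5 = 0.30.
- 30% missing: 0.3 × 0.75 = 0.225; 0.3 × 1.5 = 0.45.

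**Sampling error for comparison.** 1.96 × 1.5/√94 = 1.96 × 0.155 = 0.30. If only 75 or 66 of the 94 respond (80% or 70%), the half-width is 0.34 or 0.36. The bias can therefore be as large as the sampling error, and unlike sampling error it does not shrink with more participants.

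**Tipping point, if high scores are favourable.** The ITT mean falls to 4.5 when the non-respondent mean equals (4.5 − r × respondent mean)/(1 − r). For a respondent mean of 5.0:
- r = 0.80: (4.5 − 4.0)/0.2 = 2.5, which is 2.5 points below respondents.
- r = 0.70: (4.5 − 3.5)/0.3 = 3.33, which is 1.67 points below respondents.

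For a respondent mean of exactly 4.5, any shortfall among non-respondents takes the ITT mean below the target.

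**Direction on the scale as printed.** With 7 = completely disagree and favourably worded items, dissatisfied people score high. Take a respondent mean of 4.3 and r = 0.80:
- Non-respondents average 6: 0.8 × 4.3 + 0.2 × 6 = 4.64.
- Non-respondents average 7: 0.8 × 4.3 + 0.2 × 7 = 4.84.

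The respondent mean misses 4.5 and the ITT mean reaches it. Losing dissatisfied people then makes the printed target harder to meet.

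**The case against.** The strongest reply has five parts.

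- **The parenthesis may only describe scoring.** It may mean an average over items, as the neighbouring outcome's parenthesis says raw score, and not be a rule about who is counted. That reading is plausible, but it leaves the gap in place: a person with no survey has no items to average.
- **The article plans to assess everyone with at least 4 sessions, and ITT-FE allows early stoppers to have post-treatment data.** This stands. Stopping at session 4 to 7 does not by itself mean a missing rating, so 30% should not be read as the expected non-return. A retention effort still does not say what the ITT result is when a survey is missing.
- **Missing-data handling may sit in an analysis plan that is not shown.** This is true of detail. The article itself, however, fixes population, measure and target, and these do not match.
- **Completion rates are separate primary outcomes.** They show that people are missing. They do not change what the usability mean describes.
- **The target is a hypothesis without a stated pass/fail rule.** This also stands, and it limits the point to what may be claimed about the ITT population.

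A reader might go further and infer that usability is overstated, or that dropout will cause the target to be met. The documents do not support this. It requires non-respondents to be less satisfied, and the Limitations section links low motivation neither to unreturned surveys nor to poor ratings. On the printed anchors with favourably worded items, the effect on the target is the reverse. Item wording is not shown, so the direction cannot be settled. Nor would it help to quote a chance of about 50% that the respondent mean meets the target when the full group misses it by exactly the bias. That figure holds by construction, because the respondent mean has been placed on the target.

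**Conclusion.** The mismatch holds. Usability is promised in "primary outcome measures in all intention-to-treat (ITT) participants" but can be computed only among those who return a post-program survey, so it is a respondent mean carrying an ITT label. Bias is a plausible risk and not an established fact. Under an assumed difference of 0.75 to 1.5 points it would be 0.15 to 0.30 points at 20% missing and 0.23 to 0.45 at 30%, against a 95% half-width of about 0.30 at an assumed n of 94. These sizes rest on proxy missing rates and an assumed difference. The direction relative to 4.5 cannot be stated until the anchors and the target are reconciled: as printed, 4.5 or above lies on the disagree side. People who stop before session 4 are a separate matter, because they leave through the ITT definition and not through the survey.

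**What to change.** 1. Reconcile the printed anchors with the target of 4.5 or above, and state which end of the scale is favourable.
2. Label the usability mean as a respondent (ITT-FE) mean. Report the number responding out of all ITT participants and out of all who started therapy.
3. Add a tipping-point analysis showing how much less favourable non-respondents would have to be than respondents for the ITT population to miss the target. Claim that the ITT population meets the target only if that gap is implausibly large.
4. Optionally, as a sensitivity analysis, give the proportion rating favourably with non-return counted as not favourable. It should not replace the primary measure: it mixes attrition, already measured by the completion rates, into usability, and the article has no benchmark for it.

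The cost is analysis wording and one extra table, with no new data or participants. The downside is a possibly less favourable usability statement.

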## Discussion

### Expected Outcomes

This paper describes the methodology adopted to remotely assess and promptly treat psychiatric symptoms in a sample of patients with COVID-19 and their first-degree relatives. This digital approach is showing its innovation potential by helping to manage the psychological burden caused by the pandemic in patients with COVID-19 and their relatives.

We expect, as a prediction of our hypotheses, that the DigiCOVID protocol will result in a feasible approach; such a claim is clearly a hopeful statement, yet it is based on the quick, efficient, and technological step procedure described earlier. In terms of descriptive statistics, we might observe slight differences in terms of symptoms between patients and relatives (ie, in the posttraumatic scale, which we expect to be higher in patients than in relatives). In conclusion, we also expect the DigiCOVID protocol to be effective for both patients and their relatives in diminishing psychological distress. Future directions might involve the standardization of the DigiCOVID protocol in COVID-19 wards, as part of a complete program for the treatment of patients with COVID-19 and participants who might not have the opportunity to move to see a professional if remote visits are not possible.

To date, we are completing the recruitment, and we are expecting future and conclusive analyses to determine the efficacy and effectiveness of the protocol.

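### The usability benchmark (mean of 4.5 or more) conflicts with the printed response scale, on which high scores mean disagreement

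*Protocol article*

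**What the plan says.** The Protocol article, under Primary Outcome Measures, lists four primary outcomes. The second is usability, defined as "Usability ratings obtained post DigiCOVID via a 7-point Likert scale questionnaire (ie, mean rating of all responses"). The same entry describes the content: "this is a brief and embedded poststudy questionnaire on program satisfaction, clarity, and perceived benefits". Participants rate each sentence on anchors printed in full: "1=completely agree; 2=mostly agree; 3=somewhat agree; 4=undecided; 5=somewhat disagree; 6=mostly disagree; and 7=completely disagree". The expectation for this outcome follows directly: "we hypothesize exit survey ratings of at least ≥4.5 (SD 1.5) on the 7-point Likert scale items".

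The outcome belongs to the main analysis: "we will conduct an analysis of the following primary outcome measures in all intention-to-treat (ITT) participants". The article does not print the items. It mentions no reverse-scoring, recoding or negative item wording, in this section or elsewhere.

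**The concern.** The questionnaire asks about things a participant would normally endorse if the program were good, so agreement should be the favourable answer. On the printed anchors agreement is scored low and disagreement high, with the undecided point at 4. A floor of 4.5 therefore asks for a mean on the unfavourable side of neutral.

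This is the only one of the four primary outcomes labelled as usability, and usability is one of the three properties named in the main objective. The 4.5 figure is the only yardstick the article gives for it. If the two sentences are used together as printed, a satisfied sample would be described as falling short of expectation and a dissatisfied one as reaching it. If someone instead corrects the direction silently at analysis, the report may use a scoring direction that no document supports.

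**Working it through.** **Inputs**, all from Primary Outcome Measures: a scale of 1 to 7 with 1 the strongest agreement, 4 undecided and 7 the strongest disagreement; a benchmark mean of at least 4.5; SD 1.5; an outcome that is the plain mean of all responses. No sample size, power or significance level is attached to the 4.5, so there is no derived figure to reproduce. The check is one of direction.

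**Assumption:** items are favourably worded, so that agreeing is good.

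**Step 1. Apply the benchmark to uniform answers, and to their mirror image (8 − x).**

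| Every answer | Printed meaning | At least 4.5? | 8 − x | At least 4.5 after mirroring? |
|---|---|---|---|---|
| 1 | agree | no | 7 | yes |
| 2 | agree | no | 6 | yes |
| 3 | agree | no | 5 | yes |
| 4 | undecided | no | 4 | no |
| 5 | disagree | yes | 3 | no |
| 6 | disagree | yes | 2 | no |
| 7 | disagree | yes | 1 | no |

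As printed, every level of agreement misses the benchmark and every level of disagreement reaches it. After mirroring, the pattern is the one expected of a usability target.

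**Step 2. Mirror the benchmark.** On a 1 to 7 scale the mirror of 4.5 is 8 − 4.5 = 3.5, and the inequality turns round. A mean of at least 4.5 on a scale where high is good is the same as a mean of at most 3.5 on the printed scale.

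**Step 3. Illustrate the size.** Treat single ratings as approximately normal with mean 4.5 and SD 1.5, and cut at 3.5 and 4.5 so that the undecided category keeps its full width.

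- Agree: Φ((3.5 − 4.5)/1.5) = Φ(−0.667) = 0.252
- Undecided: Φ(0) − Φ(−0.667) = 0.500 − 0.252 = 0.248
- Disagree: 1 − Φ(0) = 0.500

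A sample exactly at the benchmark would thus have about twice as many disagreeing as agreeing ratings. With the mean at 3.5 the shares swap: about 50% agree, 25% undecided and 25% disagree. The article does not say whether the SD of 1.5 refers to single responses or to participants' means, so these shares show the direction and rough size only.

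**Step 4. Check the intended direction against the rest of the article.** The other three primary expectations are all favourable: at least 80% completing the self-reports, no adverse events from the program, and at least 70% completing the program. Expected Outcomes anticipates "that the DigiCOVID protocol will result in a feasible approach". A floor on the rating fits these only if higher means better.

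**The case against.** Four points can be made on the other side.

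*The items may be negatively worded, or reverse-scored in the full protocol.* This is possible. Items and scoring keys are commonly left out of an article, and their absence is no fault. But the article prints all seven anchors, the plain mean as the summary and the benchmark, and these do not fit together under the natural reading of the described content. What stands is that favourable wording is an assumption and must be labelled as one.

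*The 4.5 is a hypothesis, not a decision rule.* This stands. A reader might infer that the trial has a formal success criterion that would declare success on dissatisfaction. The article does not support that: it states an expected rating, with no test, significance level or pass/fail consequence. Someone holding the printed anchors would still read a mean of 2 as agreement. The error is in the stated expectation.

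*The anchors may be the misprint.* This also stands. A reader might infer that the collected responses must be reversed. If the questionnaire in use ran from disagreement at 1 to agreement at 7, reversing the responses or switching to 3.5 or less would invert correctly coded data and create the very error at issue.

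*The size could be put higher.* A reader might take P(X > 4) = 1 − Φ((4 − 4.5)/1.5) = 1 − Φ(−0.333) = 0.63 as the share disagreeing. That counts ratings between 4.0 and 4.5, which belong to the undecided category, as disagreement. With the cut at 4.5 the share is about 50%.

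**Conclusion.** The point holds as an internal inconsistency in scale direction, within a single entry of the primary outcome list. Assuming favourably worded items, the benchmark lies 0.5 points above undecided on the disagree side, so that uniform agreement misses it and uniform disagreement reaches it. The inconsistency itself is clear from the printed text. Which sentence is wrong is not, and the article alone cannot settle it. The figures of 50%, 25% and 25% are illustrative, and the conclusion does not depend on them. It should be corrected because it affects the only benchmark for a primary outcome.

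**What to change.** First, check the questionnaire actually administered, both its anchors and the polarity of each item. Then correct whichever sentence is wrong.

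- **If the printed anchors were used:** either reverse-score the favourably worded items (8 minus the response) before averaging and keep the benchmark at 4.5 or more; or keep the printed coding, put any negatively worded items in the same direction, and restate the benchmark as a mean of 3.5 or less.
- **If the administered scale ran from complete disagreement at 1 to complete agreement at 7:** correct the printed anchors, and leave the data and the benchmark unchanged.
- **If the items prove to be negatively worded throughout under the printed anchors:** the two sentences are compatible, and the article need only say so.

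State one scoring direction and use it in the questionnaire, the analysis and the report. The Results section says that preliminary analyses have already been done, so the direction should be settled from the administered form and not from the observed mean, and the correction should be documented as such.

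The cost is a look at the questionnaire and one sentence of text. No new data are needed.
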